### Plans to give access to the full protocol, participant-level data, and statistical code {31c}

We will follow the U.S. Department of Health and Human Services’ guidance on dissemination of trial information. The current study is registered under clinicaltrials.gov for public viewing and results. Results will include the following: demographic information, baseline characteristics, outcomes, analyses, adverse events, and an analysis plan. Results will be submitted no later than 1 year after the completion of final data collection. We will provide study protocol, statistical analysis plan, and the clinical study report. [name] will oversee all data storage procedures, including maintenance of security and confidentiality. Data will be gathered electronically in REDCap or will be captured on paper and entered into REDCap within 48 business hours. Because our statistician is a consultant, we have a data sharing agreement and business associate agreement in place. Although we have these agreements in place, we will strip all data of identifiable information before electronically sharing this information.

## Qualitative analysis methods

Qualitative analysis of focus group and interview data will be ongoing as data is collected. Interviews with staff and focus groups with patients will be recorded, transcribed verbatim and analyzed using a thematic approach in qualitative analysis software. An abductive coding approach will be used, beginning with a priori codes based on the frameworks used to develop interview and focus group guides, while also allowing for codes to emerge through analysis for a deeper understanding of the relationship between concepts [35]. Two study team members trained in qualitative data analysis will independently code transcripts, reviewing each other’s work and discussing discrepancies to arrive at consensus. To ensure reliability, a minimum of two coders will analyze the data, with 25% of transcripts randomly selected for independent double-coding [36].

## Oversight and monitoring

### Composition of the coordinating center and trial steering committee {5d}

This study is being conducted by Sinai Chicago with partnership between a research institution, Sinai Urban Health Institute, and a clinical entity, the Sinai Center for Diabetes and Endocrinology. The study will also be guided by two committees: a Patient Advisory Committee (PAC) and a Subject Matter Expert (SME) Committee. The PAC was formed in 2021 based on a previous study. It is comprised of seven individuals who are adults, 18 years of age or older, living with diabetes, many of which are current patients of Sinai Chicago. The PAC will meet quarterly to advise on recruitment, participant engagement, and interpretation of findings. The SME Committee is comprised of six individuals who will also meet quarterly. The purpose of this group is to advise on clinical or programmatic issues that may arise related to a patient’s care or medical situation. The SME consists of an endocrinologist, the practice manager, a nurse diabetes educator, and a community health worker.

### Composition of the data monitoring committee, its role and reporting structure {21a}

According to the 21 Code of Federal Regulations (21 CFR 312.50, 312.56, 812.40, and 812.46), a data monitoring committee is necessary for studies evaluating new drugs, biologics, or devices [37]. Because this study is not evaluating a new drug, biologic, or device, a data monitoring committee is not necessary.

### Adverse event reporting and harms {22}

The current study presents minimal risk to participants. However, potentially uncomfortable discussions may occur as it relates to participants’ previous or current medical history. All research and program staff involved in the study are responsible for reporting adverse events, including any unanticipated harms to participants, to the study PIs. We will follow the Office for Human Research Protections (OHRP) guidance for “reviewing and reporting unanticipated problems involving risks to subjects or others and adverse events” to classify adverse events as unexpected adverse events and/or serious adverse events, when applicable [38]. All adverse events will be documented in REDCap within two business days, using a detailed form specifically created to document adverse events. The form will be reviewed within two business days of the initial documentation. All documented adverse events will automatically be reported to study PIs. If an adverse event is determined to be a serious adverse event, it will be reported to the IRB as well.

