### Intervention description {11a}

In the first randomization, study participants will be randomly assigned to either the DSMT or RGM study arms after completion of the enrollment and baseline data collection. At 6 months, they will attend an in-person appointment for HbA1c lab work (if it has been more than 3 months since their last HbA1c lab work) or HbA1c point of care testing. Depending on their HbA1c, they will continue in the first randomization arm, or they will be rerandomized. Each intervention is described below.

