#### Community health worker support

CHWs will be introduced 6 months into the trial at rerandomization for participants whose HbA1c has not improved by at least one percentage point (Fig. 2. IDEA Study SMART Design). All patients paired with a CHW will be screened for social needs utilizing a standard social determinants of health (SDoH) screening tool, will receive referrals to resources to address unmet social/health needs, and will be actively navigated to health and social service resources as appropriate.

For participants originally randomized to the RGM intervention, the CHWs will focus on enhancing uptake and use of the Glooko application. During the initial in-person visit with the CHW, which will take place either at the clinic or in the participant’s home, the CHW will screen for SDoH needs, provide referrals to address unmet needs, and assess participant barriers to regularly measuring and/or reporting glucose levels using Glooko (e.g., connection issues between device and phone, barriers to transmitting information to provider). The CHW will also support the patient in overcoming barriers through individualized education, motivational interviewing, goal-setting, and trouble-shooting technological and resource challenges. Following the initial visit, the CHW will follow up with the patient at least monthly by phone for 6 months to assess adherence with RGM, trouble shoot additional barriers, and reinforce education concerning the Glooko application. The CHW will also provide active support to the participant in connecting with resources to support health and social needs. Additional in-person visits will occur during the time interval as needed.

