For participants originally randomized to the DSMT study arm, the CHW will focus on reinforcing key messages presented during DSMT sessions. During the initial in-person visit with the CHW, which will take place either at the clinic or in the participant’s home, the CHW will screen for SDoH needs, provide referrals to address unmet needs, and assess knowledge gained during the group DSMT sessions, self-efficacy to manage diabetes, and application of learnings. The CHW will support the patient in overcoming deficits in knowledge and barriers in application of knowledge via additional customized, one-on-one education sessions, motivational interviewing, goal-setting, and navigation support. Following the initial visit, the CHW will follow-up with the patient at least monthly by phone, scheduling additional in-person visits as needed for up to 6 months. Additional in-person visits will occur during the time interval as needed.

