### Strategies to improve adherence to interventions {11c}

Participants randomized to the DSMT study arm will receive a call or text message from the diabetes educator prior to each session to remind them of the class. For participants who are not able to join one of their regularly scheduled sessions, a make-up class will be offered to maximize adherence. Participants randomized to the RGM study arm will receive a call or text message from a research staff member every 2 months to provide technical assistance and encourage engagement with the application. Finally, participants randomized to the CHW study arm will receive a call or text message from the CHW prior to each one-on-one visit. We will measure intervention adherence using attendance (number of DSMT sessions attended), RGM utilization (number of blood glucose readings uploaded to Glooko and number of syncs to Sinai’s medical record system), and adherence with CHW enhancements: (1) completing an initial education session, (2) completing a SDoH screener, (3) connecting with the CHW via phone or in person at least three times over 6 months.

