### Plans to promote participant retention and complete follow-up {18b}

To minimize attrition, the research staff will call or send a text message to all study participants at least every 2 months. Those randomized to an RGM arm will receive communication from a research team member every 2 months to provide technical assistance as needed for the Glooko application. Those randomized to a DSMT arm will receive a call or text message reminder from the diabetes educator prior to each DSMT session. If a participant is unable to attend a session, the diabetes educator will offer a make-up session based on the participant’s availability. During the initial enrollment appointment, the research team will confirm or collect extensive contact information including mailing address, home and cell phone number(s), e-mail addresses, and contact information for up to three additional individuals.

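### Adverse events rest on unblinded staff reports with no uniform questioning described, while scheduled contact differs by randomized path, so posted event counts could reflect opportunity to report as well as risk

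*Protocol article*

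**What the plan says.** **Capture of events.** The section on adverse event reporting and harms {22} gives one route: "All research and program staff involved in the study are responsible for reporting adverse events, including any unanticipated harms to participants, to the study PIs". Events are recorded "using a detailed form specifically created to document adverse events", with two-business-day deadlines for entry and review. The sections on blinding {17a, 17b} leave only the statistician blinded, so the staff who report events know each participant's assignment.

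**Contact shared by all paths.** Under retention {18b}, "the research staff will call or send a text message to all study participants at least every 2 months". Everyone also has a 6-month visit ("At 6 months, they will attend an in-person appointment for HbA1c lab work") and a 12-month HbA1c follow-up.

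**Contact that depends on the path** (intervention description {11a}):

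- CHW after RGM: an initial in-person visit, after which "the CHW will follow up with the patient at least monthly by phone for 6 months".
- CHW after DSMT: an initial in-person visit, after which "the CHW will follow-up with the patient at least monthly by phone", for up to 6 months.
- DSMT: four group sessions of about 2 hours every other week, each with a reminder.
- RGM: one set-up session and outreach every 2 months for technical help. Glucose readings also pass automatically to the medical record; no such channel is described for DSMT.

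**Reporting.** Section {31c} commits to posting adverse events: "Results will include the following: demographic information, baseline characteristics, outcomes, analyses, adverse events, and an analysis plan". Neither Table 2 nor the statistical methods plan a comparison of events between paths.

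**The concern.** When staff report the events that come to their notice, the count in a path is the true rate multiplied by the chance that an event is noticed. That chance depends on how often, and how recently, someone spoke with the participant. Here it depends on the randomized assignment. The purposes stated for the routine contacts are retention, technical help and session reminders; asking about events is not among them.

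Once event counts are posted, readers will set the paths side by side whether or not the protocol plans a test. A difference could then come from contact alone, and uneven capture cannot be repaired after the data are in. The only risk named in {22} is uncomfortable discussion. Yet Table 1 admits type 1 diabetes with HbA1c from 7%, and {11a} allows insulin pumps to be synced, so glucose-related events are foreseeable. Transmitted readings could reveal them under RGM and not under DSMT.

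**Working it through.** The article states no adverse event rate and no contact total, so there is no figure of its own to reproduce. The check asks what ratio of recorded events would appear between two paths with the same true rate.

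**Contacts scheduled in months 6 to 12** (low = overlapping contacts merged; high = all counted):

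- CHW: 1 + 6 = 7, or 7 + 3 = 10
- switch to DSMT: 4 + 2 = 6, or 4 + 4 + 3 = 11
- switch to RGM: 1 + 3 = 4, or 4 + 3 = 7
- responders staying in arm: 3 for DSMT, 3 to 6 for RGM

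**Model.** Assumptions: events are uniform over months 6 to 12, and each later contact reveals an event with chance p. The article gives no p, so 0.1 to 0.5 is assumed. Let q = 1 − p. An event with k later contacts is captured with probability 1 − q^k. A set-up session or first visit at month 6 cannot reveal a later event and drops out.

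- Two-monthly contact only (months 8, 10, 12), which fits a switch to RGM: capture = 1 − (q + q² + q³)/3.
- Monthly CHW calls (months 7 to 12) that also serve as the two-monthly contact: 1 − (q + q² + q³ + q⁴ + q⁵ + q⁶)/6.
- Monthly CHW calls plus separate two-monthly contacts; later contacts by month of event are 9, 8, 6, 5, 3, 2: 1 − (q⁹ + q⁸ + q⁶ + q⁵ + q³ + q²)/6.

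At p = 0.1:

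- two-monthly: 1 − (0.9 + 0.81 + 0.729)/3 = 0.187
- CHW replacing: 1 − 4.217/6 = 0.297
- CHW adding: 1 − 3.479/6 = 0.420

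**DSMT-CHW versus DSMT-RGM, no true difference**

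| p | two-monthly | CHW replacing | ratio | CHW adding | ratio |
|---|---|---|---|---|---|
| 0.1 | 0.187 | 0.297 | 1.59 | 0.420 | 2.25 |
| 0.2 | 0.349 | 0.508 | 1.45 | 0.659 | 1.89 |
| 0.3 | 0.489 | 0.657 | 1.34 | 0.797 | 1.63 |
| 0.5 | 0.708 | 0.836 | 1.18 | 0.929 | 1.31 |

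**Sensitivity to the counting of RGM outreach.** The table treats the RGM technical call as the two-monthly retention contact, which is the natural reading of {18b}. If it is a further contact, RGM capture is 1 − (q² + q⁴ + q⁶)/3 = 0.334 at p = 0.1 and 0.891 at p = 0.5. Counting CHW contacts separately too, the ratio is 0.420/0.334 = 1.26 falling to 0.929/0.891 = 1.04. Only the mixed rule (CHW merged, RGM separate) goes below 1: 0.297/0.334 = 0.89 at p = 0.1.

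**RGM-CHW versus RGM-DSMT.** The article does not fix when sessions fall after re-randomization, so two placements are assumed, with the same model:

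- Sessions at months 6.5 to 8, two-monthly contact added on both sides: 1.74 (p = 0.1) to 1.25 (p = 0.5).
- Sessions at months 10.5 to 12, reminders counted, CHW calls merged with the two-monthly contact: 0.50 (p = 0.1) to 0.85 (p = 0.5).

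The direction is open.

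**After the fix.** If only events found at contacts common to both paths are compared, k is the same on both sides and the capture ratio is 1.0 for any p, given equal completion of those contacts.

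**The case against.** Four objections carry weight.

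1. **The article is a condensation.** It does not say that participants are never asked about events, and form content and scripts are often left to the full protocol. This stands as a limit: a reader might infer that events are caught only when staff happen to hear of them, but the text is silent on asking and does not exclude it. It also provides weekly implementation meetings {11b}, shared 6- and 12-month follow-up and ordinary clinical care. The point rests on the one route the article does state and on the stated purposes of the contacts.

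2. **No comparison of events between paths is planned.** True, so no planned analysis is invalid. Events will still be posted and can be read by path.

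3. **The gap may be smaller than scheduled.** A participant meets the contact part of CHW adherence by "connecting with the CHW via phone or in person at least three times over 6 months", so delivery may fall below monthly, and p is assumed.

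4. **RGM has its own channel.** Transmitted readings could raise RGM counts and offset part of the excess in CHW paths.

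Two stronger readings are tempting. One is that contact differs severalfold between paths in general. In months 6 to 12 it reaches 10/3 = 3.3 against DSMT responders. Over 12 months, adding three study visits, the largest ratio of a CHW path to any other is (6 + 7 + 3)/(4 + 3 + 3) = 16/10 = 1.6. Responders are also selected on 6-month HbA1c, so they are not a randomized comparator under any capture method. The other reading is that posted results would make the CHW paths look less safe. Objections 3 and 4 and the open direction of the RGM-first contrast support only that they could.

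**Conclusion.** The concern holds as a possible bias in a descriptive result, and the remedy is a cheap improvement. As written, unequal contact and RGM's separate data channel can shape adverse event counts. In the randomized DSMT-CHW versus DSMT-RGM contrast, equal true risk could appear as a ratio of about 1.6 to 1.2 if CHW calls replace the two-monthly contact, or 2.25 to 1.3 if they add to it.

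These figures assume p between 0.1 and 0.5, events uniform in time, CHW calls delivered as scheduled, RGM outreach being the two-monthly contact, and no detection through transmitted readings. Relaxing either of the last two shrinks the ratio. No direction can be claimed for RGM-CHW versus RGM-DSMT. The HbA1c analysis is not affected.

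**What to change.** - Put the same short scripted event question to every participant at the contacts all paths share: the two-monthly call (or a text that requires a reply) and the 6- and 12-month follow-up. Use the same wording in every path, covering distress from sessions, symptomatic low or high glucose, and emergency or hospital care.
- At 6 and 12 months, extract diabetes-related emergency visits and admissions from the medical record for everyone.
- Tabulate by path only the events found through these common routes. List events found in CHW or DSMT sessions, or through transmitted readings, separately with their source.

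Cost: a few minutes per existing contact, one REDCap form and an added field in a record extract, with no new visits or staff. The downside is that more events, mostly non-serious, will be recorded. If the full protocol already has uniform solicited questioning, a sentence in {22} saying so is enough.

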### Frequency and plans for auditing trial conduct {23}

The implementation team, comprised of one PI (JJ), the senior evaluator, two research specialists, the community health worker, and the diabetes educator, meet weekly to review recruitment and enrollment data. The team members responsible for recruitment and enrollment bring any points of discussion to the group. The three PIs and the senior evaluator meet bi-weekly to discuss recruitment, enrollment, and any implementation or clinical challenges as recruitment progresses.

### Plans for communicating important protocol amendments to relevant parties (e.g., trial participants, ethical committees) {25}

Any changes to the study protocol will be submitted to the Mount Sinai Hospital Institutional Review Board (IRB) and will not be implemented until IRB approval. All investigators and study team members will be made aware of changes prior to submission and will be alerted immediately upon approval. Per IRB requirements, current participants will be alerted to protocol changes should it affect their participation. Contact information for all participants are kept secure within the study database.

### Dissemination plans {31a}

Study findings have the potential to inform optimization of evidence-based approaches to address diabetes and will be shared broadly. Researchers, practitioners, policymakers, and community partners are our key target audience. Findings will be disseminated through traditional academic pathways (e.g., presentations at national and local conference, peer-reviewed journal publications). We will also utilize the Dissemination Planning Tool, developed by Carpenter et al., to ensure our research findings are disseminated in a way that will broadly reach our target audience [39]. Unlike more academic methods of dissemination, we seek to communicate findings to diverse interested parties. We will use the Dissemination Planning Tool framework and our PAC to identify what we will disseminate, to whom, how we can extend our reach, how we will convey findings and results, how to evaluate our dissemination plan, and a timeline for dissemination.

## Discussion

Diabetes affects millions of Americans each year, including a disproportionate number of racial and ethnic minorities. It is increasingly expensive to our healthcare system and to individuals, and can have severe long-term health implications. Team-based care, and specifically interventions like diabetes education, leveraging technology like RGM, and integrating non-clinical staff like CHWs, have shown promise in improving health outcomes among certain populations [40, 41]. Yet there are still gaps in our understanding of how appropriate these interventions are for the population of interest, the degree to which we can maintain fidelity, and ultimately the potential change in HbA1c among specific populations. Specifically, various social determinants of health needs, which are linked to health outcomes, may not be addressed in the traditional patient-provider relationship. The intervention components of this study provide support towards better diabetes management will also addressing SDoH needs. Findings from this study will provide a nuanced perspective of the combination and sequence of interventions that best address the needs of specific patients.

We have identified some issues when developing the protocol that are important to document for future investigators, specifically those utilizing the SMART design. First, while random assignment using software, such as REDCap, is common in the trial literature, we chose to use SNOSE and allow research participants to make the envelope selection. Our randomization process, based on the work of other researchers [30, 42], allows us to effectively randomize participants, while also following equitable research principles that empower participants [43]. Second, to prevent contamination between study arms, we have identified steps to ensure the full clinical team at the Center is aware of patients that are participating in the study (e.g., information sheets provided to staff, documentation in the EMR), and asked that they not offer DSMT or RGM to currently enrolled participants. It has been particularly challenging to explain the extent to which education can still be provided to patients during standard clinical appointments. The distinction between DSMT and informal education provided during a standard care visit is nuanced. Finally, Sinai Chicago moved to a new EMR system in September 2023, right before recruitment began. Like any other organizational change, the team has required additional time to become familiar with the system, and work with information technology staff to create the correct reports.

This study uses an innovative trial design to measure the effectiveness of varying the sequence and combination of three interventions to support diabetes management among Black and Latine patients receiving care at a safety-net hospital. Guided by a health disparities framework, we will evaluate the appropriateness (Aim 1) and fidelity (Aim 2) of these interventions, compare the effectiveness of varying the sequence to reduce HBA1c (Aim 3), and measure the extent to which CHW support can reinforce DSMT and RGM uptake and adherence (Exploratory Aim 3a). By achieving these aims, we will build the evidence for optimizing equitable diabetes management and ultimately reducing racial and ethnic healthcare disparities for patients living in disinvested urban settings.

